### **Sample Size**

To estimate the efficacy of the CIK cells therapy in a single group, a sample in the range of 20-25 will probably be adequate due to the expected population effect sizes moderate.

Consequently, we choose a sample size equal to 20 children and 20 adults. We can analyze the efficacy considering the entire group as well as also adult and children separately. Furthermore, a sample size equal to 40 is large enough to provide useful information concerning assessment of feasibility.

Below we evaluate the adequacy of a sample size equal to 40 and 20. The margin of error is also called the confidence interval and is used to describe the degree of uncertainty we have in the sample estimate.

## Confidence intervals for efficacy

To assess the efficacy of CIK cell treatment we consider the rate of patients who achieve a complete/partial molecular response following CIK cell infusion.

The two sided 95% confidence intervals for complete/partial molecular response rate from 5% - 50% for a sample size = 40 are

| Rate | Lower Limit | Upper limit | CI Width |
|------|-------------|-------------|----------|
| 0.05 | 0.006       | 0.163       | 0.163    |
| 0.1  | 0.028       | 0.237       | 0.209    |
| 0.2  | 0.091       | 0.356       | 0.266    |
| 0.3  | 0.166       | 0.465       | 0.300    |
| 0.4  | 0.249       | 0.567       | 0.318    |
| 0.5  | 0.338       | 0.662       | 0.324    |

The two sided 95% confidence intervals for the rate (5% - 50%) for patients that achieved complete/partial molecular response for a sample size = 20 are

| Rate | Lower Limit | Upper limit | CI Width |
|------|-------------|-------------|----------|
| 0.05 | 0.001       | 0.249       | 0.247    |
| 0.1  | 0.012       | 0.317       | 0.305    |
| 0.2  | 0.057       | 0.437       | 0.379    |
| 0.3  | 0.119       | 0.543       | 0.424    |
| 0.4  | 0.191       | 0.639       | 0.448    |
| 0.5  | 0.271       | 0.728       | 0.456    |

The following figure illustrates the CI width for different complete/partial molecular response rate for all patients (sample size = 40) and for each group (sample size = 20) with a two-sided confidence level equal to 95%.

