### **2.2 Secondary Objectives**

To assess the efficacy of CIK cell treatment based on:

- Reduction or disappearance of MRD
  - Achievement of complete donor chimerism,
  - Rate of and time to hematologic relapse in patients enrolled based on MRD and/or mixed chimerism
  - Progression-free and overall survival
- Molecular relapse will be assessed by STR and RT-PCR based chimerism analyses in all patients, by real time (RT)-PCR based BCR-ABL/ABL, or immunoglobulin (Ig)/T cell receptor (TCR) gene rearrangements in leukemia patients

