## Analysis

A descriptive statistics will be performed at the end of the study. An intent-to-treat principle (ITT) or per-protocol analysis will be done.

To analyze the efficacy of CIK cell treatment following factors will be considered:

- Complete and partial molecular response
- rate and duration of complete/partial molecular response following CIK cell administration at the end of CIK cell infusions and after 1 year of first CIK cell infusion
- rate of and time to non response
- rate of and time to relapse with previous partial/complete response
- Progression-Free survival (PFS) and overall survival (OS)
- Cumulative incidences of: haematological relapse/progression, deaths without relapse/progression
- Cumulative incidence of aGVHD > grade II and extensive chronic GvHD
- Median and range for the number of CIK cell dose and for cumulative dose CIK cells/kg for all patients, children and adults

- Median and range for cumulative T cells/kg according donor type (MSD, MUD,MMFD) that patient requires in the study

Complete molecular response is defined as the molecular remission: the Minimal Residual Disease not detectable (MRD < 10^-6) and Mixed Chimerism MC < 1%.

Partial response is defined as no molecular remission but not haematological relapse. Non response is defined as haematological relapse without previous or complete response.

The median of PFS and OS time will be estimated. Kaplan-Meier estimates will be used to estimate PFS probability and OS probability. Log-rank test will be used as appropriate. For PFS will be considered as events: disease progression or relapse, death without relapse/progression and secondary neoplasm. For OS death from any cause will be considered an event.

Gray-Model will be used for cumulative incidences. Patients lost to follow-up without event will be censored at the date of their last follow up evaluation.

PFS, OS and cumulative incidences will be estimated after 1 year initiation of CIK cell therapy and after 1 year until the last CIK cell infusion.

If the data meet the necessary requirements, longitudinal analysis will be conducted to explore the improvement of hematologic and immune reconstitution of leucocyte, CD3-, CD4-, CD8-, CD56-, and CD14-positive cells until the first year after begin of the CIK cells therapy.

The dynamic of cytokine profile during cell infusion and tumor escape mechanisms following CIK cell infusion will exhibit in curves over the time.

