We will use a significance level of  $\alpha = 5\%$ .

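### Section 11 analyses molecular efficacy only through response categories, and its partial response requires no fall in the marker, so the objective of reducing MRD has no analysis

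*Protocol*

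**What the plan says.** Section 2.2 lists as efficacy aims "Reduction or disappearance of MRD", complete donor chimerism, haematological relapse, and progression-free and overall survival. The synopsis gives the rate and duration of molecular response as a further, separate objective.

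In section 11, under the confidence intervals for efficacy, "we consider the rate of patients who achieve a complete/partial molecular response following CIK cell infusion", and the precision tables are built on that rate. The Analysis subsection fixes the categories:

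- Complete: "Complete molecular response is defined as the molecular remission: the Minimal Residual Disease not detectable", together with mixed chimerism below 1%.
- Partial: "Partial response is defined as no molecular remission but not haematological relapse".
- Non-response: haematological relapse without an earlier response.

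The same subsection plans progression-free and overall survival, response duration, times to non-response and to relapse, and cumulative incidences. On trajectories, "longitudinal analysis will be conducted to explore the improvement of hematologic and immune reconstitution of leucocyte, CD3-, CD4-, CD8-, CD56-, and CD14-positive cells" is all that is modelled over time; the cytokine and tumour-escape measurements are shown as curves.

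The sample-size argument is verbal: "a sample in the range of 20-25 will probably be adequate due to the expected population effect sizes moderate". The study aims state that there is no initial hypothesis and that the study is exploratory.

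**The concern.** A partial molecular response would normally imply that the disease marker had fallen. Here it implies only that the patient has not relapsed. Patients enter with a positive marker and a marrow that is not in haematological relapse, so most already fit the partial-response definition before the first infusion. Counting them as responders afterwards gives no evidence that the cells did anything to the marker.

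This trial is meant to inform a larger one. The molecular rate it carries forward would repeat information already given by the relapse analysis, and the question of whether treatment lowers residual disease would go unanswered although the measurements are scheduled.

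**Working it through.** **1. Objectives against analyses (sections 2.2 and 11).**

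| Objective | Matching analysis in section 11 |
|---|---|
| Disappearance of MRD, complete donor chimerism | Complete response |
| Haematological relapse | Time to relapse, cumulative incidence |
| Progression-free and overall survival | Kaplan-Meier |
| Reduction of MRD | None |

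**2. What the combined rate measures.** At one assessment let C be the proportion in molecular remission, P the proportion neither in remission nor in haematological relapse, and H the proportion in haematological relapse. Deaths without relapse are not placed in any category and are left aside. By the definitions, C + P = 1 - H. The protocol's worked rate of 0.4 thus means H = 1 - 0.4 = 0.6, and its tabulated range of 0.05 to 0.50 means H between 0.95 and 0.50. C and P cannot be recovered from the sum.

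**3. Status at entry.** Section 4.1 requires detectable MRD, a BCR-ABL/ABL ratio of at least 10^-4, or mixed chimerism of at least 1%. Section 4.2 excludes more than 5% malignant cells in marrow. Such a patient is generally not in molecular remission and not in haematological relapse, which is the definition of partial response.

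**4. Illustration (invented values).** Patient A goes from 10% to 1% autologous signal: log10(1/10) = -1. Patient B goes from 1% to 10%: log10(10/1) = +1. Neither is below 1%. If neither relapses, both are partial responders, although their changes differ by 2 on the log10 scale in opposite directions.

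**5. Data already scheduled (section 3.2).** During treatment, blood chimerism is obligatory monthly. Marrow is obligatory every 3 months, with MRD and BCR-ABL/ABL if appropriate. After the last infusion, chimerism remains obligatory but marrow is optional.

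**6. The plan's own precision figures reproduce.** Exact (Clopper-Pearson) 95% limits at a rate of 0.4:

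- 16 of 40: 0.249 to 0.567, width 0.318.
- 8 of 20: 0.191 to 0.639, width 0.448.

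Both match the protocol. The arithmetic is sound; the issue is what the rate stands for.

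**7. Can the loss be put as power?** Only under assumptions the plan does not make. Take a standardised within-patient change d (assumed, 0.3 to 0.8), normal changes in every patient, and two-sided 5%. Compare a one-sample t test (noncentrality d x sqrt(n)) with an exact sign test on reduced or not, where P(reduced) = Phi(d). At d = 0.5, Phi(d) = 0.691, and the sign test rejects in favour of reduction at 15 or more of 20, or 27 or more of 40.

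| d | n = 20: t / sign, % | Gain, points | n = 40: t / sign, % | Gain, points |
|---|---|---|---|---|
| 0.3 | 24.7 / 16.3 | 8.4 | 45.7 / 28.4 | 17.2 |
| 0.4 | 39.7 / 26.2 | 13.5 | 69.4 / 46.9 | 22.5 |
| 0.5 | 56.5 / 38.4 | 18.0 | 86.9 / 66.1 | 20.8 |
| 0.6 | 72.1 / 51.8 | 20.3 | 95.9 / 81.7 | 14.3 |
| 0.8 | 92.4 / 76.4 | 16.0 | 99.9 / 96.9 | 2.9 |

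Gains are taken before rounding. They run from about 3 to 23 points and depend on assumed normality and complete data. If cleared patients are tied at the best rank and relapsed or dead patients at the worst, the gain can reverse. In a simulation at d = 0.5 with 30% cleared and 20% relapsed or dead (assumed shares), a signed-rank test had power 0.29 at n = 20 and 0.52 at n = 40, against 0.37 and 0.67 for the sign test.

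**The case against.** **No planned power is lost.** A reader might take the effect size called moderate as d = 0.5 and conclude that the plan gives up about 20 points of power. The documents do not support that. They give no number or scale for the effect, no null rate and no power; the study is exploratory and sized by interval width. The plan's categories are also not reduced versus not reduced, so the table in the working does not quantify this plan. This objection stands in full.

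**Efficacy is not confined to response categories.** Survival, relapse and cumulative incidences are planned as well. True, so the point is limited to molecular efficacy. Progression counts as an event in progression-free survival, but the protocol does not define it by a marker, and an analysis of progression would still not show a fall.

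**Marker change is hard to interpret and not available in everyone.** MRD and BCR-ABL apply only where appropriate, MRD entry needs only detectability, and the assays differ. Patients enter on a threshold, which invites regression to the mean. Section 5.5 expects all such patients to relapse untreated, so zero change is not the untreated expectation. This stands, and it argues for description by entry marker rather than a pooled test.

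**A marker-trajectory analysis may sit in an analysis plan not shown here.** Possibly. But the protocol itself fixes a partial-response definition that requires no reduction, and an added analysis elsewhere would leave that definition in force.

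**Conclusion.** The point holds for molecular efficacy. As defined in section 11, complete plus partial response at an assessment equals freedom from haematological relapse, a rising marker does not disqualify a responder, and reduction of MRD has no listed analysis. This follows from the definitions and entry criteria and needs no numerical assumption beyond setting aside deaths without relapse.

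Its size cannot be given as lost power. The 3 to 23 points apply only with d between 0.3 and 0.8, normal changes and complete data; with many cleared or relapsed patients there may be no gain, or a loss. The priority is low: safety is the primary purpose, the design is exploratory, and the remedy is an addition to the analysis.

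**What to change.** In section 11:

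1. Beside the response rate, report the within-patient change from baseline in log10 of the qualifying marker (MRD, BCR-ABL/ABL ratio or percentage autologous signal), separately by entry marker. Give the median with 95% CI, overall and for children and adults, at the assessments already scheduled during treatment. Show alongside it the numbers cleared, relapsed and dead, so that the median is not read as covering patients it leaves out.
2. Extend the planned longitudinal analysis to these markers.
3. Report complete response separately from partial response. The exact-interval method of the existing tables serves for complete response alone.
4. Reconcile the definition of partial response with the objective of reduction: either state the fall that qualifies, or rename the category so that it claims no more than absence of remission and relapse. The sponsor should settle the criterion.

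No test of the change against zero and no pooled best/worst-rank test is needed.

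The cost is protocol or analysis-plan wording and one more descriptive analysis, with no new samples during treatment. The drawbacks are three assays that cannot simply be pooled, small numbers per marker within each age group, and MRD that is not serial in every patient.

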### CI width vs Rate

[figure not shown]

A sample size of 40 produces a two-sided 95% CI with a width equal to 0.318 when the complete/partial molecular response rate in the sample is 0.4. For the same response rate, a sample size of 20 patients produces a two-sided 95% confidence interval with a width equal to 0.448.

### Confidence intervals for safety

The occurrence of grade III or IV acute GvHD and extensive chronic GvHD will be considered to evaluate the safety in this study. According to published results the aGVHD > Grad II incidence for a patient with DLI treatment can be assumed 40%. We expected a lower incidence rate of aGVHD. We investigated given an incidence rate of having an aGVHD > Grad II equal to 5%, 10%, 20% and 30% then confidence interval width for different two-sided confidence levels in a sample size of 20 patients.

| N  | Rate | CI width 95 | CI width 90 | CI width 68 |
|----|------|------------------------|------------------------|------------------------|
| 20 | 0.05 | 0.247                  | 0.214                  | 0.147                  |
| 20 | 0.10 | 0.305                  | 0.265                  | 0.181                  |
| 20 | 0.20 | 0.379                  | 0.330                  | 0.222                  |
| 20 | 0.30 | 0.424                  | 0.368                  | 0.247                  |
| 20 | 0.40 | 0.448                  | 0.389                  | 0.26                   |
| 20 | 0.50 | 0.456                  | 0.396                  | 0.264                  |

The next figure represents the CI width vs different aGVHD incidence rate for one group (sample size = 20) for different confidence levels.

[figure not shown]

The estimated duration of the recruitment period is equal to 3 years according to our evaluated data in the last 10 years. Each center has treated ca. 6-7 patients per year who fulfilled the inclusion criteria defined in the protocol.

## Analysis

A descriptive statistics will be performed at the end of the study. An intent-to-treat principle (ITT) or per-protocol analysis will be done.

To analyze the efficacy of CIK cell treatment following factors will be considered:

- Complete and partial molecular response
- rate and duration of complete/partial molecular response following CIK cell administration at the end of CIK cell infusions and after 1 year of first CIK cell infusion
- rate of and time to non response
- rate of and time to relapse with previous partial/complete response
- Progression-Free survival (PFS) and overall survival (OS)
- Cumulative incidences of: haematological relapse/progression, deaths without relapse/progression
- Cumulative incidence of aGVHD > grade II and extensive chronic GvHD
- Median and range for the number of CIK cell dose and for cumulative dose CIK cells/kg for all patients, children and adults

- Median and range for cumulative T cells/kg according donor type (MSD, MUD,MMFD) that patient requires in the study

Complete molecular response is defined as the molecular remission: the Minimal Residual Disease not detectable (MRD < 10^-6) and Mixed Chimerism MC < 1%.

Partial response is defined as no molecular remission but not haematological relapse. Non response is defined as haematological relapse without previous or complete response.

The median of PFS and OS time will be estimated. Kaplan-Meier estimates will be used to estimate PFS probability and OS probability. Log-rank test will be used as appropriate. For PFS will be considered as events: disease progression or relapse, death without relapse/progression and secondary neoplasm. For OS death from any cause will be considered an event.

Gray-Model will be used for cumulative incidences. Patients lost to follow-up without event will be censored at the date of their last follow up evaluation.

PFS, OS and cumulative incidences will be estimated after 1 year initiation of CIK cell therapy and after 1 year until the last CIK cell infusion.

If the data meet the necessary requirements, longitudinal analysis will be conducted to explore the improvement of hematologic and immune reconstitution of leucocyte, CD3-, CD4-, CD8-, CD56-, and CD14-positive cells until the first year after begin of the CIK cells therapy.

The dynamic of cytokine profile during cell infusion and tumor escape mechanisms following CIK cell infusion will exhibit in curves over the time.

We will use a significance level of  $\alpha = 5\%$ .

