|                                                    | 
 
• Rate of and time to hematological relapse in patients enrolled based on MRD and/or mixed chimerism (MC), and
 
• Rate and duration of complete and partial molecular response following CIK cell infusion.
 
                                                                                                                                                                                                                                                                                                                                                                                                                                                                                                                                                                                                                                                                                                                                                                                                                                                                                                                                                                                        |

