### **3.3 Study Duration**

The estimated duration of the recruitment period will be 3 years and the total duration of the study is expected to be at least 5 years.

The study duration per patient will include study phase during CIK cell infusions and observational phase after the last CIK cell infusion.

Study phase will last until the patient reaches molecular remission (= end of CIK cell infusions), progresses or until the patient has received a maximum of 8 CIK cell infusions (maximum duration of study phase 1 year).

Observational phase will last 1 year after the last CIK cell infusion.

Additionally, CIK cell infusions will be terminated if the patient meets discontinuation criteria (see chapter 8.1). "Off-protocol" patients will be followed up for another 28 days. Patients where CIK cell infusions are discontinued, but who stay in the protocol will be followed up for 1 year (see chapter 8.1).

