**The following criteria lead to stop of additional CIK cell infusions; patients are remaining in the study:**

- Development of GVHD > Grade II
- Response to CIK cell therapy: If mixed chimerism was the reason for study eligibility, than the achievement of complete donor chimerism leads to the stop of further CIK cell infusions. If the inclusion into the study was favored by minimal residual disease detection, the achievement of MRD negativity leads to a stop of additional CIK cell infusions.

- Severe infections

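### As worded in section 11, the duration of complete/partial molecular response runs on through molecular recurrence, and its two reading times are uninformative or unequally truncated for complete responders

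*Protocol*

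**What the plan says.** The Synopsis lists as a secondary objective "Rate and duration of complete and partial molecular response following CIK cell infusion". Section 11 (Exploratory Endpoints) lists response duration. Neither place gives a reading time for duration.

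Section 11 (Analysis) gives times: "rate and duration of complete/partial molecular response following CIK cell administration at the end of CIK cell infusions and after 1 year" counted from the first infusion. The same section fixes three response categories:

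- Complete: "Complete molecular response is defined as the molecular remission: the Minimal Residual Disease not detectable", together with mixed chimerism (MC) below 1%.
- Partial: "Partial response is defined as no molecular remission but not haematological relapse".
- Non-response: "Non response is defined as haematological relapse without previous or complete response".

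It also lists, with no time limit, the rate of and time to relapse in patients with a previous partial or complete response. It does not say whether that relapse is molecular or haematological.

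Section 8.1 ends treatment on response. For patients enrolled on mixed chimerism, "the achievement of complete donor chimerism leads to the stop of further CIK cell infusions"; for those enrolled on minimal residual disease (MRD), "the achievement of MRD negativity leads to a stop of additional CIK cell infusions". Section 3.3 likewise equates molecular remission with the end of infusions, and adds: "Observational phase will last 1 year after the last CIK cell infusion".

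**The concern.** Duration of molecular response should show how long a molecular remission lasts once it is reached. Two features of the written rules work against that.

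First, the pooled complete/partial category has only one way out, which is haematological relapse. Loss of a complete remission moves the patient into partial response, inside the same pooled category. The result then largely repeats another stated objective, time to haematological relapse, and errs towards overstating durability.

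Second, if the two reading times govern duration, one falls where a complete response begins. The other leaves late responders with much less observable time than early responders. Their recorded durations would then partly reflect how many infusions they needed.

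Section 11 says the study is meant to inform a later, larger one. A durability figure that counts lost remissions as continuing response would mislead that planning.

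**Working it through.** **The plan's own figures.** The protocol gives no figure for response duration. Its precision figures concern the response rate only, and they reproduce: the exact (Clopper-Pearson) 95% interval for 16/40 is 0.249 to 0.567, width 0.318, as section 11 states.

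**Step 1: what ends the response.** Take a patient in complete response whose MRD becomes detectable or whose MC reaches 1%, with no haematological relapse.

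- Complete response no longer applies, because its definition fails.
- Non-response does not apply, because there is no haematological relapse.
- Partial response applies: there is no molecular remission and no haematological relapse.

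So complete/partial response continues. Partial response also has no onset: eligible patients (molecular relapse, marrow blasts below 5%) already meet its definition at entry.

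**Step 2: possible size of step 1.** The inputs are assumptions, not protocol figures. Time from complete response to molecular recurrence is exponential with median m; the further time to haematological relapse is exponential with median L. Deaths are ignored. With a = ln2/m and b = ln2/L:

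- truly in remission at t: exp(−at)
- recorded as in response at t: [b·exp(−at) − a·exp(−bt)]/(b − a), or (1 + at)·exp(−at) when a = b

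At t = 12 months:

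| m (months) | truly in remission | recorded, L = 2 | L = 4 | L = 6 |
|---|---|---|---|---|
| 3 | 6% | 16% | 31% | 44% |
| 6 | 25% | 37% | 50% | 60% |
| 12 | 50% | 60% | 69% | 75% |

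For m = 6 and L = 4, in units of ln2: (0.25 × 0.25 − 0.1667 × 0.125)/(0.25 − 0.1667) = 0.0417/0.0833 = 0.50. For m = 6 the recorded median is about 9, 12 and 14.5 months instead of 6.

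**Step 3: reading at the end of infusions.** Sections 3.3 and 8.1 stop infusions when remission is reached. For a complete responder the end of infusions is therefore the start of the response, and duration at that point is about zero. This does not carry over to partial response, which triggers no stop. With no defined onset, its duration at that reading would be the whole treatment period: 7 intervals of 4 to 6 weeks, or 28 to 42 weeks, for a patient given eight infusions.

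**Step 4: reading 1 year after the first infusion.** Infusion k falls at week (k − 1)·i, with i between 4 and 6 weeks (section 3.1) and k at most 8. Assume response is documented d = 4 weeks after the last infusion.

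- Cap on duration at week 52: 52 − (k − 1)·i − d
- Observation available to 1 year after the last infusion: 52 − d = 48 weeks, whatever k

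| Infusions | cap, i = 4 | cap, i = 6 | planned observation |
|---|---|---|---|
| 1 | 48 | 48 | 48 |
| 3 | 40 | 36 | 48 |
| 5 | 32 | 24 | 48 |
| 8 | 20 | 6 | 48 |

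The follow-up left unused is (k − 1)·i, which does not depend on d. After eight infusions it is 28 to 42 weeks. If loss of remission is exponential with an assumed median of 26 weeks, 15% of losses would fall within 6 weeks, 41% within 20 and 72% within 48. For assumed medians of 13 and 104 weeks the three shares are 27%, 66%, 92% and 4%, 12%, 27%.

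**The case against.** The strongest reply is that the two reading times belong to the rate, not the duration. The exploratory endpoints give a proportion at 1 year and list response duration separately with no time, and the Synopsis objective gives none either. On that reading steps 3 and 4 fall away. The Analysis sentence does join rate and duration before naming the times, so the literal text supports the concern, but the point is open. Step 1 does not depend on it.

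A second reply is that the slash may mean each category separately. Complete response taken alone ends by definition once the marker returns. That is right, and it limits step 1 to the pooled category. The protocol nowhere states marker return as an end event for duration.

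Third, the study is explorative, the analysis is descriptive, and start, end and censoring rules may be left to a statistical analysis plan. That excuses missing detail. It does not excuse a written definition under which lost remission remains response.

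From this wording a reader might infer that durability cannot be estimated at all. The documents do not support that. A cap is administrative censoring, which Kaplan-Meier handles. Follow-up for a year after the last infusion is planned, with obligatory blood chimerism within one month and then every three months. The separate time-to-relapse item would partly cover durability if relapse were defined.

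**Conclusion.** The point holds with limits. As written, pooled complete/partial response duration does not measure durability of molecular response, because molecular recurrence does not end it. With an assumed 6-month median to recurrence, 37% to 60% would be recorded as responding at 12 months when 25% are truly in remission. The size rests on assumed exponential times; the direction follows from the definitions whenever recurrence precedes haematological relapse.

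If the reading times apply to duration, then for complete responders the first is about zero and the second is capped at 48 weeks after one infusion and 6 to 20 weeks after eight, against about 48 weeks of planned observation. This assumes documentation 4 weeks after the last infusion.

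It would go too far to say that duration is zero for all responders, since partial response is unaffected by the stop rule, or that late responders must look short-lived, since that follows only if capped times are treated as complete.

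**What to change.** In section 11:

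- Report duration of complete molecular response on its own, from first documented complete response to the first of molecular recurrence (entry marker positive again, or MC at or above 1%), haematological relapse or death.
- Estimate it by Kaplan-Meier over all follow-up to 1 year after the last infusion, censoring at the last assessment of the entry marker.
- Apply the two fixed times to the response rate only.
- Do not pool partial response into this duration, and align the Synopsis objective, which names both.
- State whether time to relapse after previous response means molecular or haematological relapse, and start it at the response date.

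The change is to wording and alters no treatment rule. Its cost is that reported durations become shorter and rest on complete responders only.

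Full ascertainment should not be claimed. After the last infusion, section 3.2 makes blood chimerism obligatory but marrow assessment, including MRD and BCR-ABL, optional, and the schedule shows no blood BCR-ABL in that period. Patients enrolled on those markers may be censored early, and the protocol should state this limitation.
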